### Dependent Variables

- The primary endpoint will be PTSD, assessed using the original version of the PTSD checklist (PCL) (31). It focuses on symptoms related to a single traumatic event. The PCL is a standardized self-reported rating scale including 17 items assessing the intensity, in the last month, of 17 PTSD key symptoms. Each item uses a 5-point Likert scale ranging (from 1 = *not at all* to 5 = *extremely*). Scores consist of the total symptom severity (sum of all items going from 5 to 85) and scores of three subscales corresponding to 3 for three PTSD sub-syndromes: re-experiencing of the traumatic event, avoidance of trauma reminders, and hyperarousal.

The secondary endpoints will be:

- The coping strategies usually employed will be assessed using the Brief Coping Orientation to Problems Experienced (COPE) Inventory (32). This scale is a short version of the COPE Inventory developed by Caver and has been validated for a French population. This multidimensional instrument has 14 subscales composed of 2 items each: (1) active coping, (2) planning, (3) seeking instrumental social support, (4) seeking emotional social support, (5) focus and venting emotions (wanting to express feelings), (6) behavioral disengagement, (7) mental disengagement (distraction), (8) self-blaming, (9) positive reinterpretation, (10) humor, (11) denial, (12) acceptance, (13) turning to religion, and (14) substance use. According to guidelines, the scale might be used from a dispositional or contextual perspective. In this study, the contextual (pandemic situation) and dispositional versions will be used.- Anxiety in the last 2 weeks will be assessed during phone medical interviews using the Generalized Anxiety Disorder scale (GAD7). The scale was validated in French (33). It consists of 7 items: (1) feeling nervous, anxious, or on edge, (2) not being able to stop or control worrying, (3) worrying too much about different things, (4) having trouble relaxing, (5) being so restless that it is hard to sit still, (6) becoming easily annoyed or irritable, and (7) feeling afraid as if something awful might happen. Each item is 4-scaled: 0- never; 1- several days; 2- more than half the days; 3- nearly every day.- Anxiety about the COVID-19 crisis will be assessed during medical phone visits using a 10-point ordinal scale (from 0: free of stress to 10: maximum of stress) by answering the question: “On a scale from 0 to 10, how much stress do you feel in the context of COVID-19?”- Subjective psychic health will be assessed during medical phone visits using a 10-point ordinal scale (from 0: the worst to 10: the best) by answering the question: “How do you rate your mental health? (From 0, the worst ever to 10, the best).”- Quality of life will be assessed using the 12-Item Short-Form Health Survey (SF-12) (34), a short version of the Medical Outcomes Study Short-Form General Health Survey (SF36) (35). This self-reported questionnaire explores the quality of life related to physical, emotional, and social health. The 12 questions concern the four last weeks and investigate eight domains: physical activity, life and relationships with others, physical pain, subjective health, vitality (energy and fatigue), limitations related to the psychic status, physical condition, and psychic health. The SF-12 allows calculating a mental quality of life score and physical quality of life score.

### Data Collection Procedure

The data collection procedure is displayed in Figure 1 and Appendix (Table A).

#### Inclusion Visit and Retrospective Data Collection

Inclusion and exclusion criteria verification will be based on the patients' records. At T0, between March 17^th^ and May 10^th^, 2020, sociodemographic characteristics, psychiatric diagnoses, and lockdown conditions will be collected in medical records if available. Data will be anonymized and stored in a database. Anxiety (GAD-7) and coping scores (Brief COPE) will be collected for Saint Etienne participants during clinical visits and reported in the database.

#### Follow-Up

Lockdown assessment is proposed for participants 12 (T1), 18 (T2), and 24 months (T3) after the first lockdown.

The patients withdraw from the study at the end of their participation which will be for a maximum of 2 years.

### Bias Mitigation Measures

All consecutive patients followed up in phone visits who agree to participate in the research and meet the inclusion criteria will be included in the study to avoid selection bias.

Participants will be blinded to the study assumptions to avoid information bias. They will receive the explanations at the end of the session.

The evaluation criteria are sufficiently objective parameters to avoid any evaluation bias.

### Data Analysis

#### Sample Size

Given the clinical context of the study population, the expected prevalence of PTSD might be 30% in patients with emotion-focused coping strategies and 10% in those with problem-focused strategies. Assuming an α risk at 5% and power (1-β) of 80% (two-sided test), the number of required subjects would be 59 per group, i.e., 118 subjects in total.

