**Method/Design:**

this is a multicenter cohort study including 117 patients followed up by phone in two French geriatric psychiatry units. Sociodemographic variables, psychiatric diagnoses, lockdown conditions, coping strategies, anxiety, and depressive symptoms reported during the first lockdown will be collected retrospectively from the medical file. A first prospective assessment including personality traits, attachment type, and traumatic life events will be conducted at 12 months (T1). Follow-up visits assessing anxious-depressive symptoms and PTSD will be made 18 (T2) and 24 months (T3) after the first lockdown. The primary outcome measure is PTSD symptoms. Secondary outcomes measures are coping strategies, generalized anxiety, anxiety about the COVID-19 pandemic, and quality of life.

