The French Health Authority has recommended a follow-up of the older psychiatric patients during the lockdown period. It advocated maintaining and reinforcement of outpatient care services by favoring teleconsultation by video or phone (2).

The present study includes a population of older outpatients with psychiatric disorders followed-up by phone in French hospitals over the lockdown period.

According to previous studies, we think that: a/ Patients could experience severe anxiety symptoms during this period. This anxiety might last after lifting the lockdown restrictions. However, we hypothesize that individuals who implement problem-focused and social support-seeking coping strategies might be less anxious. Additionally, the type of coping strategies used could influence the onset of PTSD; b/ Factors such as lockdown conditions, personality traits, attachment type, and life events might affect the coping strategies.

The primary aim of the study is to investigate the link between coping strategies and the onset of PTSD after lockdown.

The secondary objectives are threefold: a/Identify the coping strategies used during the COVID-19 crisis and measure their efficiency on generalized anxiety and anxiety about the COVID-19 pandemic, b/Assess the factors which influence the coping strategies used usually and during the lockdown, especially the sociodemographic variables, the lockdown conditions, the type of personality, the attachment type, and the presence of traumatic life events, c/ Evaluate the impact of PTSD on quality of life.

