### Study Withdrawals

Patients withdraw from the study in case of refusal or inability to continue the study for medical reasons. They will not be replaced. Patients will be followed-up as part of their usual care with no substitution treatment.

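### The 118 patients behind the stated 80% power are a bare analysed number in two equal coping groups; 117 unreplaced patients, first given the PCL at 18 months, do not secure it

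*Protocol article*

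**What the plan says.** The Sample Size section assumes that "the expected prevalence of PTSD might be 30% in patients with emotion-focused coping strategies and 10% in those with problem-focused strategies". With a two-sided 5% test and 80% power it concludes that "the number of required subjects would be 59 per group, i.e., 118 subjects in total". It names no attrition rate, no inflation and no expected share of patients in each coping group.

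The Method/Design part of the abstract gives a different total: "this is a multicenter cohort study including 117 patients followed up by phone in two French geriatric psychiatry units". The same part fixes when the primary outcome is measured: "Follow-up visits assessing anxious-depressive symptoms and PTSD will be made 18 (T2) and 24 months (T3) after the first lockdown". Appendix Table A agrees, with the PCL marked at T2 and T3 only.

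On losses, the Study Withdrawals section says: "Patients withdraw from the study in case of refusal or inability to continue the study for medical reasons". It adds: "They will not be replaced".

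The Study Design section describes an observational cohort, and Bias Mitigation Measures describes consecutive inclusion of all eligible, consenting patients. Neither sets a quota or stratification by coping type.

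**The concern.** A sample size of 59 per group with no inflation is the number that must be analysed. The article uses it without any margin. It includes one patient fewer than required, foresees withdrawals, rules out replacing them, and first measures the primary outcome 18 months after the lockdown in psychiatric outpatients aged 60 and over. The equal split built into 59 per group is also outside the sponsor's control, because patients bring their own coping style.

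The comparison affected is the primary aim, the link between coping strategies and PTSD. If the study is reported as having 80% power when the achieved figure is nearer 65% to 77%, a non-significant result will carry more weight than it should.

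**Working it through.** **Inputs.** From the Sample Size section: p1 = 0.30 (emotion-focused), p2 = 0.10 (problem-focused), two-sided alpha 0.05, power 0.80, equal groups. From the abstract: 117 patients. Loss rates and unequal splits are assumptions, because the article gives neither.

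**1. Reproducing 59 per group.**

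Unpooled variance: n = (1.96 + 0.8416)² × (0.30×0.70 + 0.10×0.90) / 0.20² = 7.849 × 0.30 / 0.04 = 58.87, rounded up to 59 per group, 118 in total. This matches the article.

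Pooled variance: n = [1.96 × √(2×0.20×0.80) + 0.8416 × √0.30]² / 0.04 = (1.1087 + 0.4610)² / 0.04 = 61.6, so 62 per group, 124 in total.

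So 118 is a valid uninflated figure, from the less demanding of these two formulas.

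**2. Effect of loss, equal groups.** Power is that of the uncorrected chi-square test, found by summing the binomial probabilities of all tables with a statistic above 3.841. Losses are taken from 117 and rounded to whole patients.

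| Assumed loss | Analysed | Groups | Exact power | Unpooled formula |
|---|---|---|---|---|
| (118 as stated) | 118 | 59/59 | 80.5% | 80.1% |
| 0% | 117 | 58/59 | 79.5% | 79.8% |
| 5% | 111 | 56/55 | 77.0% | 77.7% |
| 10% | 105 | 53/52 | 74.3% | 75.5% |
| 20% | 94 | 47/47 | 70.5% | 70.5% |
| 30% | 82 | 41/41 | 64.5% | 64.7% |

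The formula column uses the unrounded number (117 × (1 − loss), halved). Exact power moves in small steps with whole patients, so differences of about a point between the columns mean nothing.

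**3. Effect of the split, 117 analysed, no loss.**

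| Emotion:problem | Groups | Exact power | Unpooled formula |
|---|---|---|---|
| 70:30 | 82/35 | 68.1% | 79.8% |
| 60:40 | 70/47 | 77.1% | 81.4% |
| 40:60 | 47/70 | 81.6% | 75.0% |
| 30:70 | 35/82 | 75.2% | 66.2% |

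The direction matters, and the two methods disagree about which direction is harmful. The exact figures describe the chi-square test. The unpooled formula is the one that yields 59.

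**4. Loss and split together.** At 20% loss (94 analysed), exact power is 57.7% for 70:30 (66/28) and 65.9% for 30:70 (28/66).

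**5. What an allowance would have looked like.** To keep 118 analysed: 118/0.95 = 124.2, so 125 enrolled; 118/0.90 = 131.1, so 132; 118/0.80 = 147.5, so 148; 118/0.70 = 168.6, so 169.

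**The case against.** The strongest reply is that nothing has been miscalculated, and that is correct: 59 per group reproduces exactly. The gap between 117 and 118 costs 0.3 points by formula and 1 point by exact enumeration, so alone it only needs reconciling.

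The attrition argument needs loss rates that the article does not give. Mild loss does mild damage: about 77% power remains at 5% loss. The exposure to loss is also shorter than 24 months suggests. T0 is taken retrospectively from records, prospective contact begins at month 12, and the PCL is scheduled twice, so one missed visit need not remove a patient. These points limit the size of the shortfall. They do not restore a margin, because with equal groups 117 analysed is already just under 80% and any further loss lowers it.

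Three stronger readings are tempting and are not supported:

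- **An uneven split necessarily lowers power.** It does not; 40:60 emotion:problem gives 81.6% by exact calculation.
- **Social support-seeking forms a third group that thins out the other two.** The Introduction does describe it as a third set of strategies, but its hypothesis is that "individuals who implement problem-focused and social support-seeking coping strategies might be less anxious". That puts it beside problem-focused coping. Nothing in the article sets up three groups, and how the Brief COPE subscales become groups may be left to the full protocol or SAP.
- **Adjusting for confounders reduces power further.** That depends on how the covariates relate to coping and to PTSD, which the article does not quantify.

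Finally, the Statistical Analysis section promises 95% confidence intervals, so imprecision would be visible to a careful reader. That softens the risk of misreading a null result but does not correct the stated power.

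**Conclusion.** The point holds and should be fixed. The calculation is right as a number analysed; the fault is that it stands as the study's size with no margin. The design as described does not secure 80% power for the primary comparison.

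With equal groups, power is 79.5% if all 117 are analysed and falls to between about 77% and 64.5% over assumed losses of 5% to 30%. With no loss, splits from 70:30 to 30:70 give between 68% and 82%. These figures rest on the article's own 30% and 10% and on an uncorrected chi-square test. The documents support neither a particular loss rate nor a particular split, so no single figure for achieved power can be given. They also do not support saying that 80% is impossible: a favourable split with little loss would reach it.

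**What to change.** Rewrite the Sample Size paragraph:

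1. Reconcile 117 with 118, stating whether 117 is a target or a count of patients included.
2. State that 80% power holds only for 118 patients with PCL data in two equal coping groups.
3. Replace the single power figure with a short table of expected power over a stated range of attrition (for example 5% to 30%) and of emotion:problem splits in both directions, naming the test used.

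The cost is one paragraph and a less favourable stated power. No extra enrolment is required. Eligibility is confined to patients followed by teleconsultation during the first lockdown, so the source population is closed, and an honest statement of power is the practical remedy.

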#### Statistical Analysis

Descriptive analyses will be conducted using Student *t*-tests for quantitative variables and Chi-square tests for qualitative variables. Kruskal-Wallis tests will be performed for non-normally distributed variables. Logistic regression models will be performed to investigate the association of coping strategies with (1) PTSD, (2) personality traits, (3) attachment type, and (4) the presence of life traumatic events. Associations between coping strategies and anxiety will be performed using linear regression models. Univariate and multivariate models will be performed to consider potential confounding factors such as environmental, psychiatric, and socio-cultural factors. Moreover, structural equation modeling including psychometric instruments will be used when appropriate.

For all analyses, a *p* < 0.05 is considered statistically significant and the 95% confidence intervals (CI) will also be provided.

## Discussion

The STERACOVID study will be the first longitudinal study to investigate coping strategies in the COVID-19 pandemic context in the psychiatric geriatric population. This study aims to determine if the type of coping strategies used has an impact on the onset of PTSD after a lockdown period. It will also determine if these coping strategies are influenced by other factors such as socio-demographics, lockdown conditions, particular personality traits, attachment type, and traumatic life events. Several studies (4, 12–14) suggested that quarantine and pandemic crises hurt mental health leading to PTSD, anxiety, and depressive symptoms.

The originality relies on the choice of the study population and the longitudinal design going from the beginning of the pandemic over the different lockdown and post-lockdown periods. Moreover, it includes several standardized and validated scales to assess PTSD, depressive symptomatology, anxiety, personality trait, attachment type, and coping strategies. We also expect to limit the recruitment bias by using phone call interviews conducted by trained psychologists.

The STERACOVID study also has some limitations. Although most assessment tools are standardized and validated scales and constructs, anxiety about COVID-19, feeling of loneliness, and subjective psychic health assessments rely on unvalidated single-item questions. Thus, for these secondary endpoints, we will conduct correlation tests with validated scales such as the GAD7 scale or the psychic health part of the SF-12 scale.

To have a sufficiently large sample, we chose not to include the types of psychiatric diagnoses in the inclusion criteria. Additionally, this will better reflect the patients seen in medical practice. However, the diagnoses classified according to ICD 10 will be collected, and the analyses will take this information into account.

This study will allow identifying the coping strategies to develop in the psychiatric population of older adults and help clinicians track patients at risk to build better care support. It will favor the implementation of more relevant coping strategies, and better lockdown living conditions to limit anxiety and PTSD.

## Ethics Statement

The studies involving human participants were reviewed and approved by the Ethics Committee of the Saint-Etienne University Hospital. This committee covers the ethical approval for the three sites of our data collection. All procedures follow the Declaration of Helsinki and the International Conference on Harmonization (ICH) Good Clinical Practice Guidelines. The patients have received an informed written information notice. The STERACOVID study is registered in the Clinical Trials database (Current Controlled Trials NCT04760795 http://clinicaltrials.gov/show/NCT04760795). The Ethics Committee waived the requirement of written informed consent for participation.

## Appendix

**Table A TA1:** Summary of follow-up data collection.

	**T0**	**T1**	**T2**	**T3**
	**Retrospective collection**	**First prospective**	**Second prospective**	**Last prospective**
	**(on patient's records)**	**collection**	**collection**	**collection**
**Moment/Actions**	**Between March 17th and May 10** ^th^ **, 2020**	**T0 + 12 months**	**T0 + 18 months**	**T0 + 24 months**
Diagnostics information	X			
Sociodemographic	X	X	X	X
Interview on living conditions	X	X	X	X
Depression				
Short GDS	X	X	X	X
GDS 15			X	X
DSM V criteria			X	X
Anxiety about the context (ordinal scale)	X	X	X^*^	X^*^
Subjective psychic health (ordinal scale)	X	X	X	X
Generalized anxiety (GAD-7)	X	X	X	X
Contextual Coping strategies (BRIEF COPE)	X	X	X	X^*^
Dispositional Coping strategies (BRIEF COPE)			X^*^	
Personality (BFI)		X		
Attachment type (RSQ)		X		
Traumatic life events		X		
Post-traumatic stress (PCL)			X	X
Quality of life (SF12)			X	X

* *To ask only if the virus is still circulating. The STERACOVID study, 2020-2022, France*.

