**Discussion:**

This study aims to determine if the type of coping strategies usually employed have an impact on the onset of PTSD after a lockdown period. It will also determine if these coping strategies are influenced by other factors such as sociodemographic variables, lockdown conditions, particular personality traits, attachment type, and traumatic life events. This study could help identify factors associated with a poorer experience of lockdowns and pandemic crisis in elderly patients followed in a psychiatric center, and guide support in future similar situations.

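### The only measure of usual (dispositional) coping is scheduled once, at the same visit as the first PCL and conditional on viral circulation; the asterisk looks misplaced, and a T2 association of usual coping with PTSD would be cross-sectional

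*Protocol article*

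**What the plan says.** **Exposure.** The Discussion paragraph of the Abstract ties usual coping to PTSD: "This study aims to determine if the type of coping strategies usually employed have an impact on the onset of PTSD after a lockdown period". The Introduction is broader: "The primary aim of the study is to investigate the link between coping strategies and the onset of PTSD after lockdown". The Abstract's Objective and the main Discussion likewise do not confine the exposure to usual coping. In the Introduction, usual coping is named separately only in secondary objective (b), as something to be explained by personality, attachment, life events and lockdown conditions.

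**Instrument.** Under Dependent Variables, "The coping strategies usually employed will be assessed using the Brief Coping Orientation to Problems Experienced (COPE) Inventory", and then "In this study, the contextual (pandemic situation) and dispositional versions will be used".

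**Schedule.** In Appendix Table A the contextual version is marked at T0, T1, T2 and T3, with an asterisk at T3 only. The dispositional version has a single mark, at T2, with an asterisk. The PCL is marked at T2 and T3 only. The asterisk means "To ask only if the virus is still circulating". The section on the inclusion visit and retrospective data collection describes T0 coping scores for Saint-Etienne participants only.

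**The concern.** A condition on viral circulation makes sense for questions about the pandemic. It makes none for a questionnaire on how a person usually copes. Staff who follow Table A as printed would put the pandemic version at T2 whatever the state of the epidemic, and would drop the usual-coping version if circulation had stopped. No other visit collects it, so both the Abstract's question and the usual-coping part of secondary objective (b) would have no data.

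The second problem is timing. The question is about impact on onset, yet the dispositional Brief COPE and the first PCL are self-reports from one visit, with no earlier PCL. The PCL covers symptoms in the last month and has an avoidance subscale. The Brief COPE includes denial, behavioural disengagement and self-blame. Current symptoms could shape the coping answers as readily as coping could shape symptoms. The adjustment for confounders described under Statistical Analysis does not settle direction.

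**Working it through.** **1. Table A, relevant rows** (conditional = carries the asterisk)

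| Item | T0 | T1 (+12 months) | T2 (+18 months) | T3 (+24 months) |
|---|---|---|---|---|
| Anxiety about the context | yes | yes | conditional | conditional |
| Contextual Brief COPE | yes | yes | yes | conditional |
| Dispositional Brief COPE | – | – | conditional | – |
| PCL | – | – | yes | yes |

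Moving the T2 asterisk from the dispositional to the contextual row would give contextual coping exactly the pattern of contextual anxiety. That is good internal evidence of a slip, though not proof.

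**2. Time from coping measure to PCL**

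- Contextual, T1 to first PCL: 18 − 12 = 6 months.
- Contextual, T0 to first PCL: 18 months (described for Saint-Etienne only).
- Dispositional, T2 to first PCL: 18 − 18 = 0 months.
- Dispositional, T2 to T3 PCL: 24 − 18 = 6 months.

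Only the pairing of T2 dispositional coping with T2 PCL lacks temporal order.

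**3. The plan's sample size.** Inputs from Sample Size: 30% vs 10%, two-sided 5%, power 80%. With unpooled variance, n = (1.960 + 0.842)² × (0.30×0.70 + 0.10×0.90) / 0.20² = 58.87, so 59 per group and 118 in total. The plan's figure reproduces. Power at 59 per group is 80.1% unpooled and 78.2% with pooled variance under the null. Steps 4 and 5 use the pooled version.

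**4. If the condition were met for only some calls** (fractions assumed, rounded down to whole patients)

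| Share with dispositional coping | n per group | Power, 30% vs 10% |
|---|---|---|
| 80% | 47 | 68% |
| 60% | 35 | 55% |
| 50% | 29 | 48% |
| 40% | 23 | 39% |

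If it is met for none, no analysis of usual coping is possible.

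**5. Using T3 to restore order.** Suppose T2 dispositional coping is related only to PTSD new at T3. Let s be the share of the assumed 30% and 10% that arises after T2, equal in both groups, with 59 per group and no dropout. For s = 0.5:

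- Still free of PTSD at T2: 59 × (1 − 0.15) = 50.1 and 59 × (1 − 0.05) = 56.0.
- New PTSD among them: 0.15/0.85 = 17.6% and 0.05/0.95 = 5.3%.
- Power: 53%.

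The same steps give 39% for s = 0.33, 32% for s = 0.25 and 17% for s = 0.10. An ordered analysis of usual coping therefore exists, but it is weak in these scenarios.

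**6. Same-visit artefact, illustration only.** Suppose current distress alone induced a correlation r between T2 coping and T2 PCL, with 117 patients. Power = Φ(atanh(r) × √114 − 1.96), which is 58%, 78% and 91% for r = 0.20, 0.25 and 0.30. These r values are assumed. The model is a simple correlation with complete data, whereas the plan states logistic regression for PTSD.

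**The case against.** The strongest reply is that the documents do not fix usual coping as the primary exposure. Only one sentence of the Abstract links it to PTSD onset. The Objective, the primary aim and the main Discussion speak of coping without that limit, and Dependent Variables lists the Brief COPE among secondary endpoints with both versions in use. This stands, and it reduces the issue to an inconsistency between that sentence and the rest.

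A reader might go further and infer that the study cannot show any coping to precede PTSD. The documents do not support that. Contextual coping at T1, and at T0 for Saint-Etienne, comes before the first PCL, and T2 dispositional coping comes before the T3 PCL. Nor do they commit the PTSD analysis to same-visit T2 data.

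A reader might also infer that the exposure will be missing for the whole cohort. That happens only for the dispositional version, and only if the footnote is applied literally and the virus is not circulating at T2.

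It can also be said that moving the dispositional Brief COPE to T1 would not prove order. T1 falls 12 months after the lockdown and no PCL is taken at T0 or T1, so PTSD could already be present. That is correct and should be acknowledged in the text.

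What remains unanswered is the misfit of the asterisk, the single conditional measurement of usual coping, and its coincidence with the first PCL.

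**Conclusion.** The concern holds for dispositional coping and PTSD found at T2, and no further. The asterisk on the dispositional row does not fit the measure and breaks the pattern of the table. Applied literally, it could remove the only data on usual coping. When collected, T2 usual coping against T2 PCL is a cross-sectional association that cannot support a statement about onset.

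The primary aim as worded in the Introduction remains answerable with contextual coping at T1. For usual coping, the ordered alternative is the T3 PCL. Counting only PTSD new after T2, its power is about 17% to 53%, against 78% for the full 30% vs 10% contrast by the same formula. That range rests on assumed shares of late-arising PTSD, equal groups and no dropout. The 58% to 91% in step 6 shows only how readily a modest same-visit correlation would reach significance; it is not evidence that such a correlation exists in this cohort.

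**What to change.** - **Table A:** remove the asterisk from the dispositional Brief COPE, and move it to contextual coping at T2 if that was intended.
- **Collection:** collect dispositional coping unconditionally, at T1 beside the BFI and RSQ if that visit is still open, otherwise at T2.
- **Exposure:** reconcile the Abstract's Discussion paragraph with the Objective, the primary aim and the main Discussion. State which Brief COPE version and visit is the primary exposure, choosing coping measured before the PCL (T1 coping to PCL at T2 and T3). If dispositional coping was not taken at T1, the contextual Brief COPE at T1 fills this role.
- **If dispositional coping stays at T2:** relate it to T3 PCL adjusted for T2 PCL, and report same-visit associations as descriptive.
- **Limitation:** state that, with no PCL at T0 or T1, PTSD already present at T1 cannot be excluded.

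The cost is wording and, at most, one questionnaire moved between existing calls: T1 slightly longer, T2 slightly shorter, no extra visit. The T3 analysis of dispositional coping would have lower power than the planned comparison, and the text should say so.
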